# ABBREVIATIONS

ANC Antenatal Care

AOR Adjusted Odds Ratio

FGD Focus Group Discussion

GBV Gender Based Violence

GEE Generalized Estimating Equations

HEP Health Extension Program

HEWs Health Extension Workers

HSDP Health Sector Development Plan

IPVp Intimate Partner violence in pregnancy

KII Key Informant Interview

OR Odds Ratio

SDGs Sustainable Development Goals

SNNPR Southern Nations, Nationalities and Peoples Region

UN United Nations

VAW Violence against Women

WHO World Health Organization

# Summary

**Background:** **Background**: A significant proportion of women in Ethiopia suffer from violence by their intimate partner during pregnancy, which has adverse maternal and newborn outcomes. Couple-focused interventions are effective in reducing and/or controlling violence between women and their intimate partners. However, interventions addressing intimate partners of the victims are not well studied, particularly in the Ethiopian setting.

**Objective**: The aim of this study is to evaluate the effect of couple-based violence prevention education on IPV during pregnancy in Hadiya Zone, Southwest Ethiopia.

**Methods and Materials**: the study will be conducted in Hadiya zone, Central Ethiopia. It is located 235 km southwest from the capital, Addis Ababa. The study will be conducted in four districts of Hadiya zone namely: Soro, Lemo, Ana Lemo and Duna districts. The study will take 8 months (6 months intervention+2 months post intervention). We will use a cluster randomized controlled trial to evaluate the effectiveness of couple-based violence prevention education (CBVPE) compared to routine care in reducing intimate partner violence during pregnancy. Sixteen kebeles will be randomly assigned to 8 interventions and 8 control groups. In the trial, 426 couples whose wives are in the first trimester will participate. Health extension workers (HEWs) will provide health education. Data will be collected at baseline and endline. All the collected data will be analyzed using SPSS or STATA version 16.0. We will use the McNemar test to appreciate the differences in outcomes of interest in both intervention and control groups before and after the intervention for categorical data. A paired t-test will be used to compare continues outcome of interest in the intervention and the control groups after and before the intervention. The GEE (Generalized Estimating Equation), will be used to test the independent effect of the intervention on the outcome of the interest. Data analysis will be performed with an intention-to-treat analysis approach. During the analysis, the effect size, confidence interval, and p-value will be calculated. All tests will be two-sided, and statistical significance will be declared at p < 0.05.

**Work plan and budget**: the project will be accomplished within 24 months. One month for participant recruitment and one month for baseline data collection; this starts in June 2022. The intervention will be implemented in 6 months, and end-line data collection will be carried out after two months of the intervention. To accomplish this project, about 276,880 birr (two hundred seventy-six thousand and eight hundred and eighty birr) will be needed for successful accomplishment.

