**6.8 sample size**

**Qualitative study:** the sample size for a qualitative study will be determined by information saturation (Dworkin, 2012). But, for planning purposes, eight (8) Focus Group Discussions (FDG)( at least two FGDs from male partners (husbands of pregnant women), two FGDs from religious leaders, two FGDs from community leaders, and two FGDs from the women's development army) will be considered. Moreover, six in-depth interviews (IDI) among pregnant women and 70**participants** will be involved in FGD, and IDI will be involved in order to explore community perspectives towards IPV in pregnancy.

**Quantitative study (CRCT):** sample size is calculated by using the following parameters: The prevalence of IPV during pregnancy (p) was  37.5% in a study conducted in Tigray, Ethiopia (Adhena et al., 2020). The expected decline of IPVp following the intervention will be 20%, with 80% power, a 95% confidence interval, an intra-correlation coefficient (ICC) variation of 0.05, a loss to follow-up of 20%, and a design effect of 2.3. Hence, the sample size is based on Stata version 16.

Design Effect (DE) = 1 + ρ (m-1)

Where,

DE=Design effect,

ρ= intra-cluster correlation coefficient = 0.05

m=number of participants per cluster = 27.

DE=1+0.05(27-1) =2.3

Attrition (20%)

=216 couples per control group and 216 couples per intervention group; sample size =432 couples, making a total of 864 participants.

Total cluster (k) = 16 kebeles (clusters)

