## 6.9 Sampling Procedure

We will use the multi-stage cluster sampling to select eligible couples in the study area. Four districts (Soro, Lemo, Analemo, and Duna) are selected randomly from the 13 districts in the zone, which consists of 116 rural kebeles. Distance and geographical accessibility will be considered to select interventions and control kebeles. At least one kebele will be left between the kebele included in the trial to serve as a buffer zone between the two arms in order to avoid information contamination. Out of 116 kebeles, 49 non-adjacent and accessible kebeles are identified. Finally, Out of 49, 16 rural kebeles—the lowest administrative units from the four districts—will be selected by simple random sampling technique for the intervention and control groups. In each cluster, there will be 27 pregnant women with their husbands who will participate, making 216 couples per arm (Figure 4).

16 clusters

Hadiya Zone (13 districts)

By simple random sampling

By simple random sampling

Soro, Lemo, Analemo and Duna districts (116 kebeles)

49 non-adjacent and accessible kebeles (clusters)

8 intervention clusters

8 control clusters

27 eligible couples per cluster

27 eligible couples per cluster control clusters

216 eligible couples per arm

216 eligible couples per arm

Figure 3: diagrammatic representation of sampling procedure

**Qualitative part:** we will deploy purposive sampling techniques for the FGD and IDI. Women support groups, male partners, religious leaders, and community leaders will be selected for the FGD. In-depth interviews (IDI) will be carried out among pregnant women until the information saturation

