**6.11 Recruitment of clusters or study participants**

Clusters included in the intervention and control groups will be selected from the four districts in Hadiya zone, namely Soro, Lemo, Ana Lemo, and Duna woredas. The couple violence prevention education will be done in eight intervention clusters of the four districts. Similarly, eight clusters from the four districts will be assigned to the control group.

**Requirement of the study participants (n=426 couples**)

Intervention group (n=213 couples)

Control group (n=213)

Control group (study 1)

8 clusters (kebeles)

n=213 couples (213 pregnant women+ 213 husbands)

GBVP education (study2)

8 clusters (kebeles)

N=213 couples (213 preg. Women+213 husbands)

Control group (study group 1)

- No intervention will be provided from the research team
- Health Extension workers in the clusters continue to provide HE on Health extension packages.

Violence prevention education (study group 2)

- Monthly couples (pregnant women and husbands) education sessions from 1^st^ trimester to term(delivery)
- Data collection at
- Baseline and end-line(two months after intervention)

 Intervention and determination of IPV experience, Knowledge, attitude and controlling towards IPV and wome’s autonomy and self-efficacy

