**6.14 Group Information**

There will be two arms or groups of information in the selected districts of the zone. There will be an intervention group (who receive couples-based violence prevention education) and a control group (who receive usual care). Hence, the clusters will be assigned into two arms by randomization. An intensive health education message will be delivered to the intervention arms based on the baseline findings. The type of unit under this study will be clusters. The four selected districts have a total of 116 clusters. Out of 49 eligible clusters, 16 clusters will be selected by simple random sampling. In each cluster, there might be 27 couples (husbands and pregnant wives) who have the potential for the health education message. Therefore, an intervention arm consists of 8 clusters, and a control arm consists of 8 clusters. There will be 27 couples per cluster, forming a total of 216 couples (216 male partners and 216 pregnant wives) in the intervention group and 216 in the control group, making 432 couples, which will be followed in the intervention period.

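### The Summary and section 6.11 give an enrolment target of 426 couples (213 per arm), but sections 6.8, 6.9 and 6.14 give 432 (216 per arm), and only 432 matches 27 couples in each of 16 kebeles.

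*Protocol*

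**What the plan says.** Two sets of numbers appear, both worded as plans.

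- **426 couples, 213 per arm.** The Summary states: "In the trial, 426 couples whose wives are in the first trimester will participate". Section 6.11 repeats the total of 426 and divides it as "Intervention group (n=213 couples" with the same number of controls. The boxes of its diagram (Figure 4) carry it through to individuals, for example "n=213 couples (213 pregnant women+ 213 husbands" in the control box.
- **432 couples, 216 per arm.** Section 6.8 ends its calculation with "216 couples per control group and 216 couples per intervention group; sample size =432 couples, making a total of 864 participants". Section 6.9 states "In each cluster, there will be 27 pregnant women with their husbands who will participate, making 216 couples per arm", and its sampling diagram (Figure 3) shows the same. Section 6.14 states "There will be 27 couples per cluster, forming a total of 216 couples" for the intervention arm, and for both arms "in the intervention group and 216 in the control group, making 432 couples".

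All of these sections work with 16 kebeles, 8 per arm. The design effect in section 6.8 is computed with 27 participants per cluster.

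**The concern.** The planned sample size is a figure that ethics reviewers, field staff and readers of the final report all rely on, and the protocol should give it once. Here the two places where a reader is likely to look first, the Summary and the recruitment section, disagree with the three sections that derive it and lay it out. The 213 is not a single slip of the pen: section 6.11 carries it through both arms and, in its diagram, through women and husbands.

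Whichever number the final report gives as planned, it will contradict part of the protocol. A reader comparing the two could wrongly conclude that recruitment stopped early or that couples were dropped.

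**Working it through.** **Inputs.** Section 6.8: IPV prevalence 37.5%, expected decline 20%, power 80%, 95% confidence, ICC 0.05, cluster size 27, loss to follow-up 20%, 16 kebeles. Section 6.24 (data processing and analysis): two-sided tests at 0.05. Sections 6.9 and 6.14: 27 couples per kebele, 8 kebeles per arm. The decline is read here as absolute (37.5% to 17.5%). A relative decline (37.5% to 30%) needs at least 1,714 couples per arm two-sided, so it cannot be the source of either target.

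**1. The plan's own figure.** Design effect = 1 + 0.05 x (27 - 1) = 2.3, as stated. Two ordinary routes then give 216 per arm:

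- Pooled two-proportion formula: 77.05, rounded up to 78 per arm; 78 x 2.3 x 1.2 = 215.3, so 216.
- Unpooled formula: 75 per arm; 75 x 2.3 / 0.8 = 215.6, so 216.

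**2. Cluster layout.**

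| Target per arm | Couples per kebele (8 kebeles) | Total | Fits 27 in every kebele? |
|---|---|---|---|
| 216 | 216 / 8 = 27 | 432 | yes |
| 213 | 213 / 8 = 26.625 | 426 | no |

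A constant 26 per kebele would give 8 x 26 = 208 per arm. So 213 needs a mix, for example five kebeles of 27 and three of 26 (135 + 78 = 213). No section describes such a mix.

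**3. Size of the discrepancy.** 432 - 426 = 6 couples, or 12 individuals; 6 / 432 = 1.4%.

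**4. Effect on power.** Pooled normal approximation, 37.5% v 17.5%, two-sided 0.05, effective n per arm = enrolled x (1 - loss) / design effect:

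| Setting | 216 per arm | 213 per arm | Gap (points) |
|---|---|---|---|
| 20% loss, design effect 2.3 | 79.0% | 78.4% | 0.6 |
| No loss, design effect 2.3 | 87.2% | 86.8% | 0.5 |
| 20% loss, design effect at the remaining cluster size (2.03 and 2.015) | 83.8% | 83.6% | 0.2 |

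Gaps are taken from unrounded powers. The level of power depends on these choices, but the gap stays below 1 point in each.

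**5. Can the arithmetic explain 213?** Carrying 77.05 unrounded gives 77.05 x 2.3 x 1.2 = 212.7, which rounds up to 213. Rounding to whole couples at the first step gives 216 directly, as in step 1. Both are possible, and section 6.8 prints none of the intermediate values.

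**The case against.** The best case for leaving the text alone has three parts.

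- **The layout may be approximate.** Section 6.14 in one place presents the 27 per cluster only as a possibility. An average of 26.6 rounds to 27, and its design effect, 1 + 0.05 x 25.625 = 2.28, rounds to the stated 2.3. This stands in part: 213 does not materially conflict with the design effect. It does conflict with the firm statements in sections 6.9 and 6.14 that each cluster will have 27 couples.
- **The detailed sections agree with one another.** Sections 6.8, 6.9 and 6.14 all give 216 per arm, and every per-kebele figure is 27. This also stands. It limits the practical harm and shows which number to keep, but it does not remove the second number from the Summary and section 6.11.
- **The difference is trivial.** It is, at 1.4% of couples. That sets the weight of the point and does not make the two figures agree.

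Some stronger readings are tempting but unsupported. A reader might infer that 213 is the raw formula result and 216 the same result rounded up to whole kebeles. The protocol says neither, and 216 also follows without any rounding to kebeles. A reader might infer that a kebele could be declared full at two different counts. No section gives a per-kebele figure other than 27, so the conflict lies only in the arm and overall totals. Nor does it affect the denominators of the participant flow: those are the couples actually screened and enrolled, and the flow diagram (Figure 5) states no planned number of couples.

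**Conclusion.** The protocol contradicts itself on its sample size: 426 couples (213 per arm) in the Summary and section 6.11, and 432 (216 per arm) in sections 6.8, 6.9 and 6.14. Of the two, only 432 equals 16 kebeles of 27 couples, and 216 per arm is also what section 6.8 states as its result. The discrepancy is 6 couples, 1.4%, and 0.2 to 0.6 points of power in the settings tried. It should be corrected as a wrong stated figure, and it gives no ground for calling the trial underpowered.

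The contradiction and the choice of 432 rest only on the stated counts and on 8 x 27 = 216. The power gap additionally assumes the absolute reading of the 20% decline and the normal approximation. How the 213 arose is unknown, and the conclusion does not depend on it.

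**What to change.** - In the Summary, replace 426 couples by 432.
- In section 6.11, replace 426 by 432 and each 213 by 216, in the text and in every box of Figure 4, including the counts of women and husbands.
- State the recruitment target once, as 27 couples in each of 16 kebeles (216 per arm, 432 couples, 864 individuals), and have the other sections refer to it.
- Do not insert 213 in section 6.8 as a value before rounding. That would record a derivation the protocol does not show. If the sponsor wishes to print the intermediate steps, they should come from its own calculation.

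The cost is a text correction. The planned 432 couples, the clusters and the analysis do not change.

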## 1. Itroduction

## 1.1 Background to the study

The most widely spread form of gender-based violence (GBV) is intimate partner violence (WHO, 2007). Intimate partner violence (IPV) refers to “any behavior within an intimate relationship that causes physical, psychological, or sexual harm to the partner” (UN, 1994). The majority of women's abuse is committed by close partners. Intimate partner violence in pregnancy is an important public health agenda and human rights violation (WHO, 2011b). Intimate partner violence is a universal phenomenon; it occurs in all settings and among all socioeconomic, religious, and cultural groups. In 2018, the World Health Organization reported that one in three women experiences physical and/or sexual violence by an intimate partner throughout the world in their lifetime, with the highest proportion in Africa, followed by Southeast Asia (WHO, 2021).

There are different types of intimate partner violence, including physical abuse, sexual assault, coercion, social isolation, emotional abuse, economic control, and deprivation (Dichter et al., 2018). Physical violence or abuse is any act or behavior such as hitting, slapping, burning, or using weapons. Sexual violence can be in the form of rape or forceful, unwanted sexual contact, whereas emotional or psychological violence can be in the form of using words or manipulation to inflict harm. The IPV takes the lion share of violence against women (WHO, 2021).

Violence during pregnancy is a possible risk to not only the pregnant mother but also to the unborn child. Studies in different countries have found that IPV during pregnancy is associated with adverse maternal outcomes including emotional distress, depression, anxiety, insufficient or inconsistent prenatal care, inadequate gestational weight gain, higher rates of smoking, alcohol use, and mortality (Mohammed et al., 2017; WHO, 2011b). IPV in pregnancy is also associated with increased health care utilization and increased health care costs (Bonomi et al., 2009; Daoud et al., 2020; Devries et al., 2010). Violated pregnant women are at higher risk of miscarriage, abruption of placentae, preterm delivery, preeclampsia, and perinatal morbidity and mortality (Alhusen et al., 2015; Belay et al., 2019; WHO, 2021).

Violence during pregnancy is a possible risk to not only the pregnant mother but also to the unborn child. Studies in different countries have found that IPV during pregnancy is associated with adverse maternal outcomes, including emotional distress. Intimate partner violence health outcomes during pregnancy are categorized into fatal and non-fatal outcomes. The fatal outcomes include homicide and suicide, whereas non-fatal health outcomes are categorized as negative health behaviors, reproductive health, and physical or mental outcomes (WHO, 2011b). Adverse maternal and newborn health outcomes are non-fatal health consequences of intimate partner violence during pregnancy (Figure 1).

Intimate partner violence outcomes (IPVp)

Fatal outcomes

Homicide

Suicide

Death

Non-Fatal outcomes

**Negative health behavior**

Antenatal alcohol and drug abuse

Smoking during pregnancy

Delayed prenatal care

**Reproductive health**

Low- birth weight

Pre-mature-birth

Low weight gain

Obstetric complications

STIs /HIV

Miscarriage

Unsafe abortion

**Physical and mental health**

Injury

Physical impairments

Physical symptoms

Depression

Anxiety

Difficulties or lack of attachment to child

Effect on the child

Disability

Figure 1: Outcomes of IPV during pregnancy, Source: World Health Organization (WHO) Information Sheet (2011).

## Studies found that women who reported intimate partner violence were significantly associated with intrauterine retardation and pre-mature labor (Martin-de-Las-Heras et al., 2019; Yu et al., 2018). Women who experience intimate partner violence during pregnancy also found that increased women’s risk of miscarriage and abortion (Afiaz et al., 2020; Alhusen et al., 2015). Intimate partner violence during pregnancy is also associated with a higher risk of antepartum and postpartum depression, anxiety, suicidal attempts, a lack of attachment to the child, and a lower level of breast feeding (Alhusen et al., 2015; Bonomi et al., 2009; Martin-de-Las-Heras et al., 2019; WHO, 2011a). Intimate partner violence is considered a tip of the iceberg, or silent epidemic, since many victims do not reveal their experience of violence from an intimate partner due to barriers (Palermo et al., 2014). Intimate partner violence has a spill-over effect. It affects not only the women and the newborns but also the family, community, society, and the nation at large (Jill Ryan and Roman, 2019).1.2 Statement of the problem

Violence against women is a phenomenon that occurs in all countries around the world (WHO, 2011b). Violence against women has been an important public health, social policy, and human rights concern since the 1993 World Conference on Human Rights and the Declaration on the Elimination of Violence against Women (UN, 1993). The majority of violence against women is committed by an intimate partner. Each year, between 1.5 and 5.3 million women are physically and/or sexually assaulted by an intimate partner (K. M. Devries et al., 2013). In the WHO multi-country study on women’s health and domestic violence against women, it was found that the prevalence of physical intimate violence in pregnancy was one percent in Japan and 28% in Peru (WHO, 2010). According to the analysis of Demography and Health Surveys and the International Violence against Women Report, the prevalence of intimate partner violence during pregnancy is lowest (2%) in Australia, Denmark, Cambodia, and the Philippines, and highest (13.5%) in Uganda. A review of clinical studies from Africa reported in 2011 showed prevalence rates of 23–40% for physical, 3–27% for sexual, and 25–49% for emotional intimate partner violence during pregnancy (Shamu et al., 2011).

Studies conducted in sub-Saharan African and Asian countries showed that the prevalence of intimate partner violence is one of the highest in Ethiopia (74%), following Jordan (87%; Muluneh et al., 2020). In a multi-country study conducted in 10 different countries, a rate ranging from 18.5 to 75.8% was reported; domestic violence by an intimate partner alone had a rate of 15.5 to 70.9%, while violence by non-partners ranged between 5.1 and 64.6% (Oche et al., 2020). Moreover, the study conducted in Eldoret, Kenya, showed that the prevalence of intimate partner violence in pregnancy (IPVp) is 34.1%. In this study, the prevalence of physical or sexual violence in pregnancy is 22.8% among the women included in the study. In this study, up to 46 (36.5%) of the survivors of IPV in pregnancy were slapped or had something that could hurt thrown at them (Luhumyo et al., 2020). The prevalence of intimate partner violence during pregnancy is the highest in Africa (Shamu et al., 2011).

A systematic review and meta-analysis conducted in Sub-Saharan Africa in 2020 indicates that the prevalence of gender-based violence, including intimate partner violence, is higher compared to other regions (Muluneh et al., 2020). In this systematic review, the prevalence of IPV in sub-Saharan Africa is 44%. Similarly, the prevalence of emotional, physical, and sexual intimate partner violence is 29.4%, 25.9%, and 19%, respectively, in Sub-Saharan Africa (Muluneh et al., 2020).

According to study findings in Ethiopia, the magnitude of intimate partner violence during pregnancy is one of the highest in the world, ranging from 26% to 65% (Abay Woday Tadesse et al., 2018, Adhena et al., 2020, Alebel et al., 2018, Alhusen et al., 2017, Berhanie et al., 2019, Gebreslasie et al., 2020).

Intimate partner violence cannot be attributed to a single factor. Individual, relational, community, and societal factors influence the experience of IPV during pregnancy, according to the ecological model of violence against women (Fulu and Miedema, 2015). In most prior studies in Ethiopia, mostly the individual factors of women and their partner were identified, including young age of women, higher age gap between couples, low educational status of women, low educational status of intimate partner, being housewife, partner alcohol use, unplanned pregnancy, previous history of miscarriage, stillbirth or pregnancy loss, and living in a rural setting, which were found to be the predictors of IPVp (Adhena et al., 2020; Al Shidhani et al., 2020; Alebel et al., 2018; Ashenafi et al., 2021; Gebrewahd et al., 2020; Lencha et al., 2019; Musa et al., 2020; Studies conducted in Ethiopia were mostly done in clinical settings and were cross-sectional. Few studies were conducted in the community with small sample sizes (Adhena et al., 2020; Gebrewahd et al., 2020; Lencha et al., 2019). A study conducted in Hossana town revealed that the prevalence of intimate partner violence was very high (58.8%) (Temesgen et al., 2019).

One of the 2030 Sustainable Development Goals (SDGs-5) aims to achieve gender equality and empower all women and girls. The specific target under this goal is the elimination of all forms of violence against women and girls. One of the specific targets is the elimination of all forms of violence against women and girls. Despite the high prevalence and growing international attention, there are limited findings on interventions to reduce or control intimate partner violence in pregnancy to achieve a sustainable development goal in 2030 in Ethiopia (UNDP, 2015).

The Ethiopian Community Health Extension Package (ECHEP) and the Ethiopian Health Sector Transformation Plan (HSTP) even did not address the issue of violence against women, despite its adverse maternal and newborn outcomes (Assefa et al., 2019; Health, 2010). Studies conducted in Ethiopia primarily focused on prevalence, correlates, and adverse outcomes, but no study has been found on the intervention to mitigate intimate partner violence during pregnancy. Therefore, this study aims to evaluate the effect of couple-based violence prevention education on intimate partner violence during pregnancy in Hadiya Zone, South West Ethiopia.

